#### Interim analysis: sample size re-estimation

To re-assess the assumed effect size, the sample size and the dropout rate in study 2, incoming data will be monitored by an independent statistician, using an unblinded interim analysis [49]. The sample size reassessment will be conducted when a pre-specified fraction of the data from the originally intended sample are collected, while data collection is ongoing [49]. Although larger data fractions may provide more accurate insights in the expected effect sizes, the current RCT should perform interim analysis relatively early to prevent excessive inclusion of participants. Therefore, an early interim analysis will be performed when 35% of the anticipated complete cases are collected (i.e., when the 6-month post-intervention data of 0.35 * 207 = 72 complete *patient cases* are collected). For the same reason, data from a surrogate timepoint, namely six months following PPI-completion, will be used for interim analysis. While the information obtained may be limited, this selected data fraction is expected to produce relevant information to reassess the effect size estimate (and hence, the sample size) compared to a priori power analysis only [49]. Importantly, this 6-month post-PPI timepoint allows for timely sample size reassessment if the expected average inclusion rate of 5 participants per week is achieved. If the actual average inclusion rate substantially deviates from this assumed inclusion rate of 5 participants per week, a more timely cut-off point for sample size re-assessment will be determined.

The Bayesian approach to sample size reassessment proposed by Wang [50] will be applied to the change score between the pretest and 6 months after intervention completion. Two comparisons will be made, one for each PPI condition (arm 1 and 2) vs. the control group (arm 3). This sample size reassessment method relies on the computation of a Bayesian posterior predictive probability under a non-informative prior distribution to estimate the number of participants (i.e., adjusted sample size) required to draw conclusions, given a pre-specified degree of statistical power and a constant Type I-error rate. In principle, the smallest effect size of the two comparisons will be used for re-estimation of the sample size, but the maximum number of participants to be included is limited at N_max_= 544, including 408 patients and 136 loved ones. This stopping rule is motivated by pragmatic considerations, as this maximum sample size is deemed maximally feasible with the anticipated inclusion rate and the duration of the inclusion phase.

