#### Study 2 (RCT): adaptive sample size design

An adaptive sample size design will be employed in study 2, estimating the required sample size prior to the study (the a priori sample size) that will be re-estimated during the trial. The proposed re-estimation will be based on results of interim analyses (the re-estimated sample size). This adaptive element in the design of study 2 is motivated by uncertainty in the anticipated effect size and dropout rate. If the actual effect size in the interim analysis is substantially different from the a priori assumed effect size, the a priori estimated sample size may be inadequate to achieve the desired level of statistical power in decision-making. Therefore, interim analysis will be applied to (a) reassess the adequacy of the a priori computed effect size; (b) reassess the initially assumed dropout rate; and (c) replace the a priori sample size by a re-estimated sample size based on these reassessed parameters if needed.

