#### A priori sample size

The a priori sample size in study 2 is based on the anticipated change in positive mental health between baseline and one-year treatment follow-up at the clinical setting in the intervention conditions compared to the control group. Compared to arm 3 (i.e., TAU), a medium effect size of Hedges’ g = 0.45 is assumed for both PPI arms followed by a mental health treatment (i.e., arms 1 and 2). The effect size of Hedges’ g = 0.45 is conservatively estimated based on prior studies about PPI effectiveness [21, 45], assuming an overlap in treatment mechanisms when combining a PPI with a subsequent mental health treatment. The Mental Health Continuum – Short Form (MHC-SF) is defined as the primary outcome [46], which is justified in the section on ‘’Data collection’’. Using a pretest-posttest design for this primary outcome, the required sample size was estimated at 207 patients, including 69 patients per treatment arm under a 5% Type I error rate, 80% statistical power, and an equal allocation ratio. While the PPI + mental health treatment arm including loved ones (arm 2) is expected to yield a larger effect size than the PPI + mental health treatment arm without loved ones (arm 1), the actual difference between both effect sizes is unknown due to the novelty of the inclusion of loved ones. In the absence of previous studies, we will conservatively assume identical effect sizes for both arm 1 and arm 2, which can be compared to arm 3 (TAU) with a sufficient degree of certainty. In addition, we still aim to compare arm 1 to arm 2 exploratively, knowing that these specific comparisons may not be adequately powered. Assuming a 35,5% attrition rate between baseline and the 1-year follow up measurement following treatment completion based on previous findings [47, 48], a total sample size of 207/(1–0.355) = 321 participants (*n* = 321) is required, yielding 107 patients per treatment arm. Since the second arm involves one loved one per patient, this arm will contain 214 participants. Thus, a total sample size of 428 participants will be required, including 321 patients and 107 loved ones.

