## Data analysis

All analyses of (cost-)effectiveness will be performed in accordance with the Intention-To-Treat (ITT) principles, meaning that data from all participants will be analysed according to the study condition to which they were initially assigned, regardless of adherence [94]. Assessment of baseline inequalities between study conditions will be performed and followed up, if needed. Due to the longitudinal nature of study 1 and study 2, dropout and other processes causing missing data are expected [95]. Appropriate missing data handling techniques will be applied after assessment of the magnitude, mechanisms, and patterns of missing data [96]. A one-sided alfa of 0.05 will be applied in both studies. Since multiple comparisons between RCT arms will be performed in study 2, this significance level of 0.05 will be adjusted to manage Type I error probability, using the Holm-Bonferroni method [97].

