### Clinical effectiveness

#### Primary analyses

The primary clinical analyses aim to examine whether the eHealth PPI has a significant clinical effect on positive mental health (i.e., MHC-SF), which will be evaluated in the RCT of study 2. The primary analysis will be an Analysis Of Covariance (ANCOVA), which aims to compare the three independent RCT conditions on positive mental health scores at the 12-month post-PPI measurement, with the pre-PPI measurement serving as a covariate.

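### The sample-size re-estimation is computed on the raw 6-month change score, while the primary test is a baseline-adjusted ANCOVA, so the new N does not target the power of the test to be run.

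*Protocol article*

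**What the plan says.** All references are to the Protocol article.

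- **Interim analysis: sample size re-estimation.** A Bayesian predictive-probability method with a non-informative prior "will be applied to the change score between the pretest and 6 months after intervention completion". It is done for each PPI arm against TAU, and in principle "the smallest effect size of the two comparisons will be used for re-estimation of the sample size", with a cap of 408 patients (544 participants). The look takes place at 72 complete patient cases, and the article itself calls the 6-month time point a surrogate.
- **Primary analyses.** "The primary analysis will be an Analysis Of Covariance (ANCOVA", comparing the three arms on the MHC-SF 12 months after the PPI, with the pre-PPI score as covariate.
- **A priori sample size.** g = 0.45 for each PPI arm against TAU, described as a pretest-posttest calculation, giving "69 patients per treatment arm under a 5% Type I error rate, 80% statistical power, and an equal allocation ratio". No pre-post correlation is stated.
- **Purpose.** The interim section and the Research ethics section both give avoiding unnecessary recruitment as a reason for the early look.

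**The concern.** A re-estimated N is useful only if it is the N that gives the planned power for the test that will be done. Under randomisation the change score and the ANCOVA estimate the same mean difference between arms at a given time point, but with different residual variances. The change score fixes the slope on baseline at 1; ANCOVA estimates it. If the interim calculation takes its variance from the change score, it sizes the trial for a less precise analysis than the one planned.

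At stake is the size of the trial: how far N moves from 321 towards the 408-patient cap, and how many patients (and, in arm 2, loved ones) are recruited without being needed for the primary test.

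**Working it through.** **1. The plan's own figures.** Without baseline adjustment, n per arm = 2[(z_α + z_β)/g]².

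- One-sided 5%: 2[(1.645 + 0.842)/0.45]² gives 62.
- Two-sided 5%: 2[(1.960 + 0.842)/0.45]² gives 78 (79 by the exact t-test).

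The a priori section gives no sidedness; the Data analysis section says "A one-sided alfa of 0.05 will be applied in both studies". Neither version gives 69. An unstated correlation can produce it: at two-sided 5%, r = 0.33 with the ANCOVA factor (1 − r²), or r = 0.55 with the change-score factor 2(1 − r); at one-sided 5%, r = 0.44 with the change-score factor. So 69 cannot be verified, but it is not shown to be wrong. The other figures reproduce: 207/0.645 = 321; 0.35 × 207 = 72, or 24 per arm; 408 × 4/3 = 544.

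**2. Variance of the two estimators at one time point.** Let the baseline and follow-up SDs be s0 and s1.

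- Change score: s0² + s1² − 2r·s0·s1.
- ANCOVA residual: s1²(1 − r²).
- Difference: (s0 − r·s1)², which is never negative.

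At a common time point the change score is therefore never the more precise of the two, apart from the one degree of freedom spent on the covariate. With s0 = s1 the ratio of required N is 2(1 − r)/(1 − r²) = 2/(1 + r).

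**3. Size over an assumed range of r.** For illustration, suppose ANCOVA needs 69 per arm, that is 321 enrolled at 35.5% attrition. The enrolment implied by the change score is 3 × 69 × ratio/0.645.

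| r (assumed) | N ratio 2/(1+r) | Per arm | Enrolled | Against cap of 408 |
|---|---|---|---|---|
| 0.3 | 1.54 | 106 | 494 | above |
| 0.4 | 1.43 | 99 | 458 | above |
| 0.5 | 1.33 | 92 | 428 | above |
| 0.6 | 1.25 | 86 | 401 | below |
| 0.7 | 1.18 | 81 | 378 | below |
| 0.8 | 1.11 | 77 | 357 | below |

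The ratio does not depend on the anchor of 69; the counts do. At r = 0.5 the change-score variance is 2(1 − 0.5) = 1, the same as ignoring baseline altogether; below 0.5 it is worse than that.

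**4. Different correlations at 6 and 12 months.** The interim uses 6-month data and the test uses 12-month data, so the relevant ratio is 2(1 − r6)/(1 − r12²). With r12 = 0.5:

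- r6 = 0.60: 0.80/0.75 = 1.07
- r6 = 0.65: 0.70/0.75 = 0.93
- r6 = 0.70: 0.60/0.75 = 0.80

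If the correlation falls enough, the inflation disappears or reverses. The mismatch remains.

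**5. Side note on the minimum rule.** With 24 per arm and both true effects 0.45 (SD units), the two estimates share the TAU arm. Their difference has SD √(2/24) = 0.289, and the expected minimum is 0.45 − 0.289 × √(2/π)/2 = 0.45 − 0.115 = 0.335. A simulation gave the same value.

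**The case against.** **The direction is not guaranteed.** The factor 2/(1 + r) assumes equal variances and one correlation for both time points. Step 4 shows that a falling correlation can remove or reverse the excess. This stands, and it is why the size is given as a conditional range. It does not rescue the change score: the result is then an accidental offset, not a calculation aimed at the final test.

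**The change score matches the a priori calculation, and the Bayesian method's details are not shown.** Both are fair. The full protocol may contain a conversion. But the article states both choices explicitly, and as stated they differ.

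Three stronger readings are tempting and are not supported.

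- *That the dropout rate seen by 6 months will replace the planned 35.5% and so pull N down.* The article says only that it will "reassess the initially assumed dropout rate", while the a priori section is "Assuming a 35,5% attrition rate between baseline and the 1-year follow up measurement following treatment completion". Nothing says the early rate is substituted, and how it is projected forward is detail that an article commonly leaves to the full protocol.
- *That using the smaller effect is an error and a pooled effect should replace it.* The rule is deliberate, qualified as applying in principle, limited by the cap, and protects both contrasts with TAU, which the Discussion calls the most important. The article also expects arm 2 to do better and assumes equality only for want of prior studies. Pooling would be a trade-off: it could leave the weaker arm underpowered.
- *That the re-estimated N is wrong in both directions.* This depends on the dropout reading and falls with it.

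**Conclusion.** The point holds in a limited form. The re-estimation is specified on the pretest-to-6-month change score and the primary test on a baseline-adjusted 12-month score, so the new N is not aimed at the power of that test. With equal variances and the same r at both time points, N is overstated by 11% to 54% for r from 0.8 to 0.3 (33% at r = 0.5). No r is stated, so the range is an assumption, and a lower correlation at 12 months would shrink or reverse the excess. The cap at 408 patients, 27% above 321 (408/321 = 1.27), limits what any overstatement can cost. The minimum rule adds some further upward pressure on N, since two equal effects of 0.45 yield an expected minimum of about 0.335, but that is a defensible design choice and not part of the fault. This is a free improvement, not a flaw that invalidates the trial.

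**What to change.** Before the interim data are unblinded, specify that the predictive-probability calculation uses the baseline-adjusted (ANCOVA) difference of each PPI arm from TAU at 6 months, with its residual SD, in place of the raw change score. In projecting to the 12-month test, allow for a lower correlation with baseline than at 6 months, for example by showing the re-estimated N over a stated range of 12-month correlations. The smallest-effect rule and the cap can stay as they are.

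The cost is a changed formula for the independent statistician and a sentence or two in the plan. No new data are needed: Table 2 already has the MHC-SF collected from patients before the PPI and at 6 months.

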### Research ethics

General research ethics will guide the implementation of our studies. From an ethical perspective, all incoming patients will have an opportunity to be assessed for study eligibility during this inclusive recruitment process, regardless of their initial complaints and demographic characteristics. All research activities in the proposed O4U-system adhere to current participant privacy regulations within Dutch mental healthcare. The e-consent file will be established in accordance with the latest regulatory requirements in Dutch research trials involving humans [109], including a mandatory reflection period for participants after receiving study information and before providing consent. In the e-consent file, all patients and their loved ones will be asked to confirm whether they had enough time to decide upon study participation.

Following the General Data Protection Regulation (GDPR), every participant retains the right to withdraw from the proposed studies at any given time. In addition, all participants hold the GDPR-compliant right to be forgotten at any time, meaning they can no longer be contacted for the study or any follow-up research. However, the researchers retain the formal right to use a participant’s anonymized data collected prior to study withdrawal. The related software and platforms used to implement the eHealth PPI and research measurements comply with contemporary patient privacy regulations and procedures regarding (digital) e-consent. Following completion of the waiting period, all patients will receive an official intake for mental health treatment at the mental health clinic, regardless of whether the patients in the PPI conditions have actually completed the eHealth PPI.

Lastly, the proposed sample size re-assessment in the interim analysis of study 2 aims to prevent including too many participants. However, by the time this interim analysis is conducted, there may still be a minor risk of more participants being included than necessary to obtain statistical power. In this case, all excess participants are allowed to complete the eHealth PPI, but will no longer receive unnecessary follow-up measurements. This approach aims to minimize participant burden, while preserving statistical power.

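### The interim can move the final sample size in either direction, but the final ANCOVA carries no matching adjustment, so the 5% error rate is not guaranteed if only one PPI arm works

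*Protocol article*

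**What the plan says.** All places are in the Protocol article.

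- **Planning** (A priori sample size): Hedges' "g = 0.45 is assumed for both PPI arms followed by a mental health treatment", giving "69 patients per treatment arm under a 5% Type I error rate, 80% statistical power, and an equal allocation ratio". That is 207 complete cases, raised to 321 patients for 35.5% attrition.
- **Interim** (Interim analysis: sample size re-estimation): an independent statistician makes an unblinded comparison at 35% of complete cases, which is 72 patients or about 24 per arm. It uses the change from baseline to 6 months after the PPI. The smaller of the two PPI-versus-TAU effects sets the new sample size, with a cap of 408 patients. The method is said to operate "given a pre-specified degree of statistical power and a constant Type I-error rate". The timing of the interim may move if inclusion is faster or slower than expected.
- **Downward adaptation** (same section and Research ethics): one purpose is to avoid including too many patients. If too many are already in, "all excess participants are allowed to complete the eHealth PPI, but will no longer receive unnecessary follow-up measurements". No minimum is stated.
- **Final test** (Primary analyses): "The primary analysis will be an Analysis Of Covariance (ANCOVA), which aims to compare the three independent RCT conditions on positive mental health scores" at 12 months, with baseline as covariate.
- **Alpha** (Data analysis): "A one-sided alfa of 0.05 will be applied in both studies". Because several arms are compared, "this significance level of 0.05 will be adjusted to manage Type I error probability, using the Holm-Bonferroni method".

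**The concern.** A test that pools all patients as if the sample size had been fixed keeps its nominal level only if the sample size does not depend on the observed treatment effect. Here it does, in both directions.

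The exposed case is one effective arm and one ineffective arm. Once the effective arm is rejected, Holm tests the other at the full one-sided 0.05. The ineffective arm usually shows the smaller interim effect, so its own early result sets the final number. If that result is high by chance, the sample is cut and the lucky early patients keep a large share of the final estimate. If it is low, more patients are added and dilute it. Both movements favour rejection.

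At stake is a false claim for the second PPI arm. The two separate arm-versus-TAU contrasts are there to support exactly that kind of claim.

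**Working it through.** **1. The plan's own figures.** 207/(1 − 0.355) = 321 patients; 0.35 × 207 = 72 interim cases, or 24 per arm, leaving 69 − 24 = 45 per arm. The cap of 408 patients gives 408 × 0.645 = 263 completers, about 88 per arm. All of these reproduce.

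The 69 per arm does not follow from the stated inputs alone. With n = 2(z₁₋α + z₀.₈)²/g² and g = 0.45:
- one-sided 0.05: 2(1.645 + 0.842)²/0.2025 = 61.1, so 62 per arm;
- two-sided 0.05: 2(1.960 + 0.842)²/0.2025 = 77.5, so 78 per arm.

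A baseline correlation r of about 0.34, which is not stated, would give 78(1 − r²) = 69. The 69 is therefore not shown to be wrong, and nothing below depends on its derivation.

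**2. Fixed design as reference.** With 69 per arm and Holm at one-sided 0.05, simulated family-wise error is 4.5% under the global null and 4.9-5.0% when one arm works. Without adaptation, Holm is adequate.

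**3. Adaptive design.** Inputs taken from the article: 24 per arm at the interim, smaller effect drives n, cap 88 per arm, pooled final test, Holm at one-sided 0.05. Inputs assumed, because the article does not give them:
- the floor per arm;
- the correlation ρ between 6-month change and baseline-adjusted 12-month outcome;
- a target probability of 0.8 and a planning alpha of one-sided 0.025;
- known variance;
- n goes to the cap when the target cannot be reached.

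Two rules were tried: plugging in the observed effect, and a flat-prior predictive probability. For the second, with interim statistic z₁ on n₁ = 24 per arm and critical value c,

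PP(n) = Φ{ [z₁√(n/n₁) − c] / √((n − n₁)/n₁) },

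and n is the smallest value between floor and cap with PP(n) ≥ 0.8.

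**4. Plausible ρ.** Let a be the correlation of baseline with 6 months, b of baseline with 12 months, and k of 6 with 12 months. Then ρ = (k − ab)/√[2(1 − a)(1 − b²)].
- a = b = k = 0.5: 0.25/√0.75 = 0.29.
- a = 0.6, b = 0.5, k = 0.8: 0.50/√0.60 = 0.65.

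So 0.3-0.7 is a reasonable range and ρ = 1 is an extreme.

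**5. Results.** Error for the ineffective arm when the other arm is clearly effective (range over the two rules):

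| Floor per arm | ρ = 0.3 | ρ = 0.5 | ρ = 0.7 | ρ = 1.0 |
|---|---|---|---|---|
| 25 | 5.1-5.2% | 5.3% | 5.5-5.6% | 6.0-6.4% |
| 60 | 5.0-5.1% | 5.1% | 5.2% | 5.3-5.4% |
| 69 (increase only) | 5.0% | 5.1% | 5.1% | 5.2-5.3% |

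A separate simulation with a floor of 25 gave 5.1-5.7% at ρ = 0.3-0.7. With g = 0.45 in the working arm and a floor of 25, the four columns become 5.0%, 5.2%, 5.4-5.5% and 5.8-6.2%. Under the global null the family-wise error stays at 4.5-4.8%.

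If an unreachable target sends n back to 69 instead of the cap, and shrinkage is barred, the figures are 4.95-5.06%. Some rules compatible with the text therefore do not exceed 5% to any meaningful degree.

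**6. With fixed stage weights.** Under the predictive rule with a floor of 25, the combination test gives 4.9-5.0% when one arm works and 4.5% under the global null.

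**The case against.** **The interim is not an efficacy analysis.** A reader might infer that a strong interim result turns the re-estimation into an unadjusted efficacy stop at 35% of the data. The documents do not support that. No efficacy boundary or early claim is stated, and the interim looks at 6-month change whereas the final test is at 12 months. This part of the objection stands.

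**A floor near 24 per arm is extreme.** At 5 patients per week, 72 to 72/0.645 = 112 patients are enrolled in about 14 to 22 weeks. Adding 8 weeks of PPI and 26 weeks of follow-up puts the interim at about week 48 to 56, with 240-280 patients randomised. That is 240 × 0.645/3 = 52 to 280 × 0.645/3 = 60 completers per arm, or as few as 43 if the 5 per week includes loved ones. With floors of 43, 52 and 60, the error at ρ of 0.3-0.75 is 5.1-5.6%, 5.0-5.4% and 5.0-5.2%. This largely stands and is why the size must be given as a range. It does not remove the point: Research ethics allows follow-up of patients already included to stop, so the number analysed can fall below the number recruited, and no floor is written down.

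**The quoted phrase describes a cited method.** That source may restrict the sample size or adjust the critical value; this cannot be checked here, and the full protocol may say more. A reader might infer that the cited method is itself faulty; nothing here shows that. What remains is that the article fixes the adaptation, its driver, the cap, the final test and the alpha correction, and the analysis as stated carries no safeguard across.

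**Conclusion.** The point holds as a modest one. The article pairs an unblinded sample size change, up or down and without a floor, with a plain pooled ANCOVA and a Holm step meant only for several arms. As stated, that combination does not guarantee 5% when one PPI arm works and the other does not.

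The family-wise error is about 5.0-5.7% at ρ of 0.3-0.7, about 5.0-5.2% with a floor near 60 per arm, and up to about 6.4% only with a floor near 24 and ρ near 1. There is no excess under the global null. A flat statement that the error exceeds 5%, or a headline of 6%, would go beyond the documents. The figures depend on the assumed floor, correlation, target probability, planning alpha and handling of unreachable targets.

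**What to change.** Before the interim data are unblinded, pre-specify for each PPI-versus-TAU contrast

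Z = √(24/69) Z₁ + √(45/69) Z₂,

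where Z₁ is the 12-month ANCOVA statistic from the interim cohort and Z₂ the same statistic from all remaining patients. Apply Holm to the two resulting one-sided p-values. If the interim timing moves, fix the weights at the newly planned split before unblinding. Three conditions should be written with it:
- only the interim cohort's outcome data inform the re-estimation;
- that cohort stays in 12-month follow-up whatever the interim shows;
- a minimum final sample size above the interim cohort is stated.

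The cost is plan wording and a few lines of code, plus a small efficiency loss when the final number differs from plan. At the cap, the effective size is [√(24/69)·√24 + √(45/69)·√64]² = (2.889 + 6.461)² = 87.4 instead of 88 per arm. At 60 per arm it is (2.889 + 4.845)² = 59.8. The loss grows if the sample is cut close to 24.

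If the plain ANCOVA is kept, make the planned 321 patients the minimum and state that a residual excess remains (about 5.0-5.3%). That option nearly removes the problem but does not guarantee 5%.
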